## Abstract

**Introduction:**

Preclinical studies provided a strong rationale for a pathophysiological link between cell-free hemoglobin in the cerebrospinal fluid (CSF-Hb) and secondary brain injury after subarachnoid hemorrhage (SAH-SBI). In a single-center prospective observational clinical study, external ventricular drain (EVD) based CSF-Hb proved to be a promising biomarker to monitor for SAH-SBI. The primary objective of the HeMoVal study is to prospectively validate the association between EVD based CSF-Hb and SAH-SBI during the first 14 days post-SAH. Secondary objectives include the assessment of the discrimination ability of EVD based CSF-Hb for SAH-SBI and the definition of a clinically relevant range of EVD based CSF-Hb toxicity. In addition, lumbar drain (LD) based CSF-Hb will be assessed for its association with and discrimination ability for SAH-SBI.

**Methods:**

HeMoVal is a prospective international multicenter observational cohort study. Adult patients admitted with aneurysmal subarachnoid hemorrhage (aSAH) are eligible. While all patients with aSAH are included, we target a sample size of 250 patients with EVD within the first 14 day after aSAH. Epidemiologic and disease-specific baseline measures are assessed at the time of study inclusion. In patients with EVD or LD, each day during the first 14 days post-SAH, 2 ml of CSF will be sampled in the morning, followed by assessment of the patients for SAH-SBI, co-interventions, and complications in the afternoon. After 3 months, a clinical follow-up will be performed. For statistical analysis, the cohort will be stratified into an EVD, LD and full cohort. The primary analysis will quantify the strength of association between EVD based CSF-Hb and SAH-SBI in the EVD cohort based on a generalized additive model. Secondary analyses include the strength of association between LD based CSF-Hb and SAH-SBI in the LD cohort based on a generalized additive model, as well as the discrimination ability of CSF-Hb for SAH-SBI based on receiver operating characteristic (ROC) analyses.

**Discussion:**

We hypothesize that this study will validate the value of CSF-Hb as a biomarker to monitor for SAH-SBI. In addition, the results of this study will provide the potential base to define an intervention threshold for future studies targeting CSF-Hb toxicity after aSAH.

**Study registration:**

ClinicalTrials.gov Identifier NCT04998370. Date of registration: August 10, 2021.

## Background

After an aneurysmal subarachnoid hemorrhage (aSAH) up to two-thirds of patients develop aSAH-related secondary brain injury (SAH-SBI), which negatively influences clinical outcome [1]. SAH-SBI typically occurs between day 4 and 14 after aneurysm rupture and manifests as angiographic vasospasms of large cerebral arteries (aVSP) [2], delayed cerebral ischemia (DCI) with radiologic demarcation of ischemic brain areas, or clinically diagnosed delayed ischemic neurologic deficits (DIND) [3]. There is an unmet need for early identification of patients at high risk for SAH-SBI. Clinical scores [4, 5], radiological scores [6–8], and day-to-day assessment with transcranial doppler sonography [9, 10] are widely used in a clinical setting, despite showing a limited accuracy [11]. Additionally, there is no clinically established biomarker to reliably monitor for SAH-SBI.

The pathophysiology of SAH-SBI is believed to be multifactorial involving macro- and microvascular dysfunction, neuroinflammation, neuronal apoptosis, and pathological electrical activity of the brain [1]. After the rupture of an intracranial aneurysm, blood components extravasate and disseminate into the cerebrospinal fluid (CSF), forming a subarachnoid hematoma. The subsequent decomposition of this hematoma, which is accompanied by erythrocytolysis, liberates cell-free hemoglobin into the CSF (CSF-Hb) [12]. CSF-Hb has been shown to reflect specific features of SAH-SBI through nitric oxide depletion and oxidative processes after heme liberation in ex vivo assays and translational in vivo models. Therefore, CSF-Hb is suspected of being one principal driver of the pathophysiological processes underlying SAH-SBI (Fig. 1) [12–14].

**Fig. 1 Fig1:**
[figure not shown]
The pathophysiological concept of cell-free hemoglobin toxicity after aneurysmal subarachnoid hemorrhage: Usually with a delay of a few days after aneurysm rupture, hemoglobin (Hb) tetramers are released from lysing erythrocytes of the subarachnoid hematoma. The dimerization of Hb and hence the smaller molecular size allows for a delocalization across tissue barriers into vulnerable anatomical sites, such as the wall of blood vessels or the brain parenchyma. Within these compartments Hb exerts its toxicity through nitric oxide depletion and heme toxicity. (Illustrations by [name])

In a single center observational study, we found strong evidence for a positive association between daily measured EVD based CSF-Hb and the occurrence of SAH-SBI [12]. EVD based CSF-Hb showed a discrimination ability for SAH-SBI in general (AUC: 0.89 [0.85–0.92]), but also for the 3 clinical subgroups aVSP (AUC: 0.89 [0.82–0.93]), DCI (AUC: 0.88 [0.81–0.93]) and DIND (AUC: 0.89 [0.84–0.92]) that considerably exceeded the accuracy of established methods [12]. Receiver operating characteristic (ROC) analyses for SAH-SBI, aVSP, DCI, and DIND also generated preliminary insights into the clinically relevant toxicity range of EVD based CSF-Hb [12].

The strong underlying pathophysiological rationale, the preliminary clinical evidence for a positive association and high discrimination ability, and its easy measurability, position CSF-Hb as an attractive biomarker to monitor for SAH-SBI. The primary objective of this prospective international multicenter cohort study is to validate the positive association between EVD based CSF-Hb and SAH-SBI during the first 14 days post-SAH. Secondary objectives include the assessment of the discrimination ability of EVD based CSF-Hb for SAH-SBI and the definition of a clinically relevant range of EVD based CSF-Hb toxicity. Also, LD based CSF-Hb will be assessed for its association with and discrimination ability for SAH-SBI.

## Methods/design

### General study design and population

The HeMoVal study is designed as a prospective international multicenter observational study. The study population consists of patients admitted to a tertiary care center due to an aneurysmal subarachnoid hemorrhage.

#### Eligibility criteria

Participants fulfilling all of the following *inclusion* criteria are eligible for the study:

a. Age ≥ 18 years.

b. Hospital admission due to an aneurysmal subarachnoid hemorrhage (diagnosis radiologically confirmed)

The presence of any of the following *exclusion* criteria will lead to exclusion of the participant:c.Non-aneurysmal subarachnoid hemorrhage (eg. trauma, perimesencephalic subarachnoid hemorrhage).d.Participation in another study with CSF sampling or an interventional medical product within the 30 days preceding and during the present study.e.Previous enrollment into the current study.

#### Enrollment

Patients with SAH admitted to one of the study centers will be screened for study inclusion as soon as possible after hospital admission (usually within 24 hours) by a member of the clinical study team at the respective center. The screening will be based on the initial CT imaging of the head to confirm SAH and vascular imaging (CT-Angiography, MR-Angiography, Digital Subtraction Angiography) for detection of a ruptured aneurysm. In patients fulfilling the inclusion and not meeting any of the exclusion criteria, informed consent will be obtained as required per local regulations.

#### Withdrawal and discontinuation

A study participant who discontinues study participation prematurely for any reason is defined as dropout. This may happen when:a patient who was incapable of giving informed consent at the time of inclusion does not agree to participate in the study once she/he is capable of giving consent. Any samples collected until the participant’s study withdrawal will be destroyed. Any data collected until the participant’s study withdrawal will be destroyed or, if destruction is not possible as in the study database, de-identified by removal of the patient ID. De-identified data will not be included in the analysisa patient who was incapable of giving informed consent at the time of inclusion and who remains permanently unable to judge and his/her legal representative does not agree to study participation Any samples collected until the participant’s study withdrawal will be destroyed. Any data collected until the participant’s study withdrawal will be destroyed or, if destruction is not possible as in the study database, de-identified by removal of the patient ID. De-identified data will not be included in the analysisa patient withdraws his/her study participation. Any samples and data collected until study withdrawal will remain coded for the analysis. It is not possible to anonymize the data and samples upon withdrawal as this would involve disproportionate effort.

### Study objectives

#### Primary objective

The primary objective of this study is to evaluate the strength of association between EVD based CSF-Hb (measured in the morning) and SAH-SBI (assessed in the afternoon of the same day) during the first 14 days post-SAH.

#### Secondary objectives

The secondary objectives are to investigate:Temporal profiles and dependence of EVD and lumbar drain (LD) based CSF-Hb:i.The temporal profile (day 1 to day 14 post-SAH) of EVD based CSF-Hb in the EVD cohort.ii.The temporal profile (day 1 to day 14 post-SAH) of LD based CSF-Hb in the LD cohort.iii.Difference (per day and overall) between EVD and LD based CSF-Hb from day 1 to day 14 post-SAH.iv.The strength of association between EVD based CSF-Hb (measured in the morning of day 1 to 14 post-SAH) and aneurysm location (assessed at study inclusion), hematoma volume (assessed at study inclusion), presence of intraventricular hemorrhage (assessed at study inclusion) and day post-SAH in the EVD cohort.v.The strength of association between LD based CSF-Hb (measured in the morning of day 1 to 14 post-SAH) and aneurysm location (assessed at study inclusion), hematoma volume (assessed at study inclusion), presence of intraventricular hemorrhage (assessed at study inclusion) and day post-SAH in the LD cohort.EVD based CSF-Hb and SAH-SBI, aVSP, DCI, and DIND in the EVD cohort:i.The temporal profiles (day 1 to day 14 post-SAH) of SAH-SBI, aVSP, DCI, and DIND in the EVD cohort.ii.The temporal profiles (day 1 to day 14 post-SAH) of EVD based CSF-Hb stratified by the presence or absence of SAH-SBI, aVSP, DCI, or DIND in the EVD cohort.iii.The strength of association between EVD based CSF-Hb (measured in the morning) and aVSP, DCI, and DIND (assessed in the afternoon of the same day) during the first 14 days post-SAH in the EVD cohort.iv.The discrimination ability of EVD based CSF-Hb (measured in the morning) for SAH-SBI, aVSP, DCI, and DIND (assessed in the afternoon of the same day) during the first 14 days post-SAH in the EVD cohort.v.The discrimination ability of EVD based CSF-Hb (measured in the morning) for the first occurence of SAH-SBI, aVSP, DCI, and DIND (assessed in the afternoon of the same day) during the first 14 days post-SAH in the EVD cohort.vi.The discrimination ability of EVD based CSF-Hb (measured in the morning of day X) for the first occurence of SAH-SBI, aVSP, DCI, and DIND (assessed in the afternoon of day X + 1) during the first 14 days post-SAH in the EVD cohort.vii.The discrimination ability of EVD based CSF-Hb (measured in the morning) for SAH-SBI, aVSP, DCI, and DIND (assessed in the afternoon of the same day) during day 4 and day 14 post-SAH in the EVD cohort.LD based CSF-Hb and SAH-SBI, aVSP, DCI, and DIND in the LD cohort:i.The temporal profiles (day 1 to day 14 post-SAH) of SAH-SBI, aVSP, DCI, and DIND in the LD cohort.ii.The temporal profiles (day 1 to day 14 post-SAH) of LD based CSF-Hb stratified by the presence or absence of SAH-SBI, aVSP, DCI, or DIND in the LD cohort.iii.The strength of association between LD based CSF-Hb (measured in the morning) and SAH-SBI, aVSP, DCI, and DIND (assessed in the afternoon of the same day) during the first 14 days post-SAH in the LD cohort.iv.The discrimination ability of LD based CSF-Hb (measured in the morning) for SAH-SBI, aVSP, DCI, and DIND (assessed in the afternoon of the same day) during the first 14 days post-SAH in the LD cohort.v.The discrimination ability of LD based CSF-Hb (measured in the morning) for the first occurence of SAH-SBI, aVSP, DCI, and DIND (assessed in the afternoon of the same day) during the first 14 days post-SAH in the LD cohort.vi.The discrimination ability of LD based CSF-Hb (measured in the morning of day X) for the first occurence of SAH-SBI, aVSP, DCI, and DIND (assessed in the afternoon of day X + 1) during the first 14 days post-SAH in the LD cohort.vii.The discrimination ability of LD based CSF-Hb (measured in the morning) for SAH-SBI, aVSP, DCI, and DIND (assessed in the afternoon of the same day) during day 4 and day 14 post-SAH in the LD cohort.EVD based CSF-Hb and 3-months follow-up status:i.The strength of association between EVD based CSF-Hb during the first 14 days post-SAH and chronic hydrocephalus at 12 weeks follow-up in the EVD cohort.ii.The strength of association between EVD based CSF-Hb during the first 14 days post-SAH and functional outcome (GOSE, mRS) at 12 weeks follow-up in the EVD cohort.LD based CSF-Hb and 3-months follow-up status:i.The strength of association between LD based CSF-Hb during the first 14 days post-SAH and chronic hydrocephalus at 12 weeks follow-up in the LD cohort.ii.The strength of association between LD based CSF-Hb during the first 14 days post-SAH and functional outcome (GOSE, mRS) at 12 weeks follow-up in the LD cohort.

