### Statistical analysis

Statistical analyses will be performed in R in an R studio environment on a Mac computer operating system [15]. The entire statistical code will be written by two authors (KA and [name]). The reviewing statistician (UH) will have an overview of the entire code. A second review statistician will independently reproduce the primary analyses. No interim analysis will be performed. The final analysis will be conducted after completion of the study, i.e. when every patient has reached the 12 weeks follow-up, and data has been cleaned by the central data monitor. For analysis, the study population will be divided into the following three populations: EVD cohort (at least one CSF-sampling via an EVD), LD cohort (at least one CSF-sampling via an LD), full cohort (all included patients, irrespective of their CSF-sampling status). The null hypothesis is that there is no association between the concentration of EVD based CSF-Hb and the occurrence of SAH-SBI during the first 14 days post-SAH in the EVD cohort. The confirmatory alternative hypothesis is that there is an association between the two. The primary analysis evaluates the strength of association between SAH-SBI (dependent binary variable) and EVD based CSF-Hb (independent continuous variable) in the EVD cohort based on a generalized additive model (GAM) with day post-SAH as continuous covariable (non-linear spline-fit with 4 knots), and repeated observations in the same patients over time and each study site accounted for with random intercepts. The likelihood ratio test *p*-value will be used to test the null hypothesis of no effect of the biomarker at a 5% significance level. In the primary analysis, no adjustment of the significance level for multiple testing is needed. Detailed description on summary statistics, secondary and safety endpoint analyses can be found online in the statistical analysis plan (10.5281/zenodo.5556317). For secondary analyses, no level of statistical significance will be defined. Instead, the results of secondary analyses will be interpreted based on the level of evidence (*p* < 0.001: very strong evidence; *p* < 0.01: strong evidence; *p* < 0.05 evidence; *p* < 0.1 weak evidence; *p* > 0.1: no evidence [16]) and confidence intervals will be provided. No confirmatory claims will be based on the secondary analyses. The results of the study will be reported according to STROBE guidelines for reporting of observational research [17].

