The HeMoVal study will enroll all patients who are diagnosed with aSAH at admission, thus ensuring that start of CSF sampling from a newly introduced EVD or LD is possible at each day of the 14-day monitoring period. For the statistical analysis, the cohort will be stratified into an EVD cohort (at least one CSF sample obtained via an EVD), LD cohort (at least one CSF sample obtained via an LD), and a full cohort (all patients admitted with an aSAH). Distinguishing between EVD and LD cohorts anticipates potential differences in the temporal profiles of EVD and LD based CSF-Hb, and hence their association to and discrimination ability for SAH-SBI. Despite the anatomical communication between the intraventricular and lumbar CSF spaces, substantial differences in the protein levels of samples obtained from the two compartments were described in patients with multiple sclerosis [19]. The full cohort serves as reference for the generalizability of the finding in the EVD and LD cohort to the overall aSAH population.

The strength of association between CSF-Hb and SAH-SBI, aVSP, DCI, and DIND will be quantified using a GAM. GAMs blend properties of generalized linear models with additive models [20]. The data structure of the HeMoVal study is characterized by repeated CSF-Hb measurements and clinical assessments (aVSP, DCI, DIND, and hence the composite outcome SAH-SBI) in the same subjects during the 14 day monitoring period, for which we will adjust with a random intercept. In the same way, there will be adjustment for potential intracluster correlation per study site. In addition, based on the results of our pilot study, we expect a non-linear relation of SAH-SBI, aVSP, DCI, and DIND to the day post-SAH with a peak between post-SAH day 8 and 12 [12]. A GAM provides the flexibility to incorporate these properties, including smooth functions of covariates, while maintaining some degree of explainability [20].

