In this study, a timed imaging protocol was deliberately avoided since it would have had to be performed at high frequency due to the variability of the temporal occurrence of aVSP and DCI and would therefore have been associated with an unacceptable additional burden for the patients (e.g., radiation exposure during CTA, transport risk of intubated patients). Moreover, it would not have been a compelling substitute for clinically indicated imaging in the setting of neurologic deterioration. Thus, in the HeMoVal study, we follow the real clinical situation with imaging according to clinical indication, which increases the variability of the results, but also their generalizability.

The HeMoVal study has the potential to strengthen the evidence for a positive association between CSF-Hb levels and the occurrence of SAH-SBI. In the future, CSF-Hb may serve as a biomarker to monitor for SAH-SBI. CSF processing and photospectrometry based measurements constitute easy to conduct procedures, which could be readily implemented as point-of-care test. The HeMoVal study is intended to provide generalizable data on the discrimination ability of CSF-Hb for SAH-SBI and thus to provide the basis to define an intervention threshold. Final choice on a clinical intervention threshold will additionally depend on the individual burden and the economic costs associated with false-positive and false-negative results.

Given the hypothesized causal pathophysiological link, CSF-Hb also represents a potential drug target. Targeting CSF-Hb through intrathecal application of the Hb-scavenger haptoglobin offers both preventive and therapeutic potential [12, 13]. By complexation, haptoglobin was shown to compartmentalize cell-free Hb in the CSF space, thereby inhibiting Hb delocalization into the brain parenchyma or smooth muscle cell layer of cerebral arteries [13]. Both ex vivo and in vivo, haptoglobin exhibited an anti-vasospastic effect on cerebral arteries [12, 13]. Haptoglobin also protected from lipid-peroxidation in an ex vivo assay for quantification of the oxidative potential [12]. The HeMoVal study will provide more generalizable information on the clinically relevant toxicity range of EVD and LD based CSF-Hb through ROC analyses for SAH-SBI, aVSP, DCI, and DIND. Those results are expected to inform the development of haptoglobin as a CSF-Hb targeting therapeutic in patients after aSAH.

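### The ROC objectives do not condition on day post-SAH, so the AUC can exceed same-day discrimination and a pooled CSF-Hb cut-off can perform very differently on peak-risk days

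*Protocol article*

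**What the plan says.** Under Secondary objectives, item iv for the EVD cohort is "The discrimination ability of EVD based CSF-Hb (measured in the morning) for SAH-SBI, aVSP, DCI, and DIND". The endpoint is read a few hours after sampling, and the window is the full monitoring period. Items v and vi keep the 14-day span but take the first occurrence of each endpoint, on the same day and on the next day respectively. Item vii repeats item iv over a shorter window: "assessed in the afternoon of the same day) during day 4 and day 14 post-SAH in the EVD cohort". The LD cohort has the same four items. The Abstract names the method: "discrimination ability of CSF-Hb for SAH-SBI based on receiver operating characteristic (ROC) analyses". No item is per day, although the EVD-LD difference in the same section is requested both per day and overall.

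The primary GAM in Statistical analysis is fitted "with day post-SAH as continuous covariable (non-linear spline-fit with 4 knots". The Discussion gives the reason: "we expect a non-linear relation of SAH-SBI, aVSP, DCI, and DIND to the day post-SAH with a peak between post-SAH day 8 and 12". The Background places SAH-SBI typically between days 4 and 14. The Fig. 1 caption describes the marker's own delay: "Usually with a delay of a few days after aneurysm rupture, hemoglobin (Hb) tetramers are released from lysing erythrocytes".

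On use, the Discussion intends the study to give generalizable discrimination data and "thus to provide the basis to define an intervention threshold". It also expects the ROC analyses to inform the toxicity range. Statistical analysis refers the detail of secondary analyses to a SAP that is not shown here, and states that no confirmatory claims will rest on them.

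**The concern.** If marker and outcome both follow the calendar, early patient-days (low CSF-Hb, few events) act as easy controls for events around days 8-12. The AUC then credits CSF-Hb with information that the day post-SAH already carries. At the bedside the day is known, so the useful question is how well CSF-Hb separates patients on a given day.

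The cut-off has the same difficulty. A single concentration chosen on pooled days has pooled sensitivity and specificity, and these need not hold on the days when risk is highest. The toxicity range and the basis for a threshold are to come from these ROC analyses, which the primary test's day adjustment does not reach.

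**Working it through.** **The document's own figure.** The pilot AUC for SAH-SBI, 0.89 (0.85-0.92), cannot be reproduced. The article gives no CSF-Hb distribution, daily prevalence or number of patient-days, and does not say how days were handled.

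**Inputs from the article.** Windows of days 1-14 and 4-14; outcome peak at days 8-12; delayed hemoglobin release.

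**Assumed inputs (not in the documents).**
- Curve g(t) = exp(-0.5 × ((t - 10)/3)²), with equal numbers of patients sampled each day.
- Daily prevalence p(t) = 0.02 + (P - 0.02) × g(t), with P = 0.20 or 0.45.
- Mean CSF-Hb μ(t) = R × g(t), with R = 1, 2 or 3 within-day SD.
- Within a day, CSF-Hb is normal with SD 1, and case-days lie δ higher. Within-day AUC = Φ(δ/√2), so δ = 0, 0.545 and 1.190 for AUC 0.50, 0.65 and 0.80.

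**Formula.** Pooled AUC = Σᵢ Σⱼ w₁(i) × w₀(j) × Φ((μᵢ + δ - μⱼ)/√2), where w₁ and w₀ are the shares of case-days and control-days falling on each day.

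**Why the shift arises.** With P = 0.45, days 1-3 hold 3% of case-days but 27% of control-days; days 8-12 hold 62% and 28%. Take R = 2 and δ = 0. A day-10 case (μ = 2) is compared with a day-1 control (μ = 2 × exp(-4.5) = 0.022). The case ranks higher with probability Φ(1.978/1.414) = 0.92, although the marker separates nobody within a day.

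**Pooled AUC (three values: R = 1 / 2 / 3).**

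| Within-day AUC | Days 1-14, P = 0.20 | Days 1-14, P = 0.45 | Days 4-14, P = 0.20 | Days 4-14, P = 0.45 |
|---|---|---|---|---|
| 0.50 | 0.561 / 0.607 / 0.637 | 0.579 / 0.640 / 0.678 | 0.534 / 0.563 / 0.583 | 0.546 / 0.584 / 0.611 |
| 0.65 | 0.698 / 0.724 / 0.733 | 0.714 / 0.752 / 0.769 | 0.677 / 0.690 / 0.694 | 0.687 / 0.709 / 0.719 |
| 0.80 | 0.830 / 0.835 / 0.827 | 0.842 / 0.856 / 0.855 | 0.816 / 0.815 / 0.805 | 0.823 / 0.830 / 0.825 |

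With R = 0 the pooled and within-day AUC are equal. Using p(t) as the score, so that only the day counts, the AUC is 0.683 (P = 0.20) or 0.738 (P = 0.45) over days 1-14, and 0.625 or 0.667 over days 4-14.

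**Sensitivity to the curve.** With widths of 2.5-3.5 days and prevalence 0.01 + (0.15 or 0.35) × g(t), a within-day AUC of 0.50 reads 0.55-0.70 over days 1-14 and 0.53-0.64 over days 4-14.

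**Cut-off.** With P = 0.45 and R = 2, take the cut-off that maximizes the Youden index over days 1-14.
- Within-day AUC 0.65: cut-off 1.36, pooled sensitivity 0.72 and specificity 0.66. Day-10 specificity is Φ(1.36 - 2) = 0.26 and sensitivity 0.88. Day-4 sensitivity is 1 - Φ(1.36 - 0.271 - 0.545) = 0.29.
- Within-day AUC 0.80: cut-off 1.74, pooled sensitivity 0.79 and specificity 0.76. Day-10 specificity is Φ(1.74 - 2) = 0.40 and sensitivity 0.93.
- With R = 1, day-10 specificity is 0.43 and 0.57 at the two AUCs; with R = 3 it is 0.13 and 0.25.

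**The case against.** The strongest reply is that a pooled AUC is a legitimate quantity. The study's hypothesis is that released hemoglobin drives injury. If so, part of the day effect runs through CSF-Hb, and matching on day may remove signal as well as confounding. This stands: the pooled AUC should be kept, and calling it wrong would go too far.

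The second reply is that the article lists objectives and leaves the ROC computation to a SAP that is not shown. This stands in part. The SAP may already add a day-adjusted measure. But the multi-day target is fixed in the objectives here, beside a primary model that adjusts for day.

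Third, there are mitigations. Item vii drops days 1-3, and the planned CSF-Hb profiles stratified by endpoint status would show same-day separation descriptively. The analyses are non-confirmatory, and the article says a final threshold will also weigh the burden and cost of false results. These lower the stakes, but none gives a same-day AUC or the performance of a cut-off on a given day.

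A reader might also infer that patient-days will be treated as independent in the confidence intervals. The article does not support that. It says only that intervals will be provided, and it handles repeated observations explicitly in the GAM.

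**Conclusion.** The point holds as a gap in what is estimated. Every discrimination objective spans several days without conditioning on day, although the article expects marker and outcome to move with day. Item vii reduces the effect but does not remove it.

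The size depends on assumed curves. Over days 1-14 the upward shift is about 0.06-0.18 at a within-day AUC of 0.50, 0.05-0.12 at 0.65 and 0.03-0.06 at 0.80. Over days 4-14 it is 0.03-0.11 at 0.50 and 0.03 or less at 0.80. It is nil without a shared time course. The calculation uses daily prevalence and so does not model the first-occurrence items v and vi.

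Three stronger readings are not supported:
- That all discrimination analyses cover days 1-14: item vii does not.
- That the AUCs are inflated as a matter of fact: the article gives neither time course in numbers, and a pooled AUC answers a different question.
- That the pilot's 0.89 is an artefact of time: no case with within-day AUC 0.50 exceeded 0.70.

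Nor do the documents show in which direction a toxicity range would move. They support only the narrower statement that a pooled cut-off's performance need not carry over to a given day. The change should be made, but the primary hypothesis test is unaffected.

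**What to change.** For items iv-vii in both cohorts, keep the pooled AUC and add to the analysis plan:

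1. A day-adjusted AUC. Compare each case-day only with control-days at the same day post-SAH and average over days weighted by case-days, or use a covariate-adjusted ROC curve with day as the covariate.
2. The AUC of day post-SAH alone, over the same window and patient-days, as the benchmark that CSF-Hb has to beat.
3. Sensitivity and specificity of any proposed CSF-Hb cut-off by prespecified day stratum, reported before the cut-off is used as the basis for a toxicity range or threshold. Strata could follow the article's own landmarks, for example days 1-3, 4-7, 8-12 and 13-14.

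Day is already recorded, so no new data are needed. The cost is a little more analysis, wider intervals for day-specific estimates (especially on early days and in the LD cohort if it is small) and probably a lower AUC than the pooled one. If the SAP already contains these measures, a sentence in the results paper saying which AUC is reported would suffice.
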